### Offspring clinical assessment

The height and weight of the neonate will be measured and the growth reference charts of the Swiss Society of Paediatrics will be used.^38 39^ Gestational age will be determined using either the date of the last menstrual period or the first-trimester ultrasound dating. Clinical chemistry (including glucose, total cholesterol, LDL-cholesterol, HDL-cholesterol, triglycerides, insulin, uric acid, hs-CRP, mi-RNA) will be assessed at birth using cord blood. We will explore the profile of circulating non-coding RNAs in offspring of women with GDM and without GDM to assess the involvement of epigenetic mechanisms in cardiovascular alterations.^40^ Blood for future analyses will be stored in a biobank. The clinical data assessed as part of the usual care of the offspring and potentially influencing the outcomes of interest will be collected.

## Sample size

Assuming that LVMI will be 30 g/m^2.7^(SD: 4.5) in children of mothers without GDM^60^compared with 32 g/m^2.7^(SD: 4.5) in children of women with GDM, the required sample size is 80 women with GDM and 80 women without GDM to have a statistical significant difference with a power of 80% and an alpha-level set at 0.05 (two sided). This sample size is also sufficient to observe statistical significant differences in cIMT at birth if we assume that cIMT at birth is 0.44 mm (SD: 0.04)31 in newborn of women with GDM and 0.42 mm (SD: 0.04) in newborn of women without GDM. In the worst case scenario, we could lose up to 20% of participants between inclusion and delivery. Therefore, we plan to include 100 pregnant women with GDM and 100 women without GDM.

## Statistical analysis

The association between exposure (GDM/no GDM) and the (continuous) outcomes will be estimated with linear regression analyses. Adjustment for potential confounding factors (maternal characteristics such as age, body mass index, blood pressure, socioeconomic status, personal history of CVD, treatment for GDM during pregnancy) will be done. To assess the direct and indirect (through mediators) effects of GDM on the outcomes, causal mediation analyses will be conducted.^61 62^ Because LGA is a potential mediator of the effect of GDM on offspring outcomes,^63^ analyses adjusted on birth weight will be conducted to estimate the indirect effect of GDM on the outcomes (figure 1). We will also consider the effect of treatment which will be treated as a mediator between GDM, LGA and outcomes.

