## Objectives

Our objectives are to assess the effect of GDM on offspring’s cardiovascular health early in life, namely on (1) the surrogate markers of CVD and atherosclerosis at birth (LVMI and cIMT) (primary outcomes) and (2) the cardiovascular structure and function during the foetal period and potential neonatal cardiovascular risk factors (secondary outcomes).

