At the second visit (V2), between the 30th and 34th weeks of gestation, a foetal echography will be performed to assess the fetal cardiac structure (including LVMI) and function, the fetomaternal circulation, and the hepatic volume.

In women with GDM, information about treatment and blood glucose measurements will be recorded during the whole pregnancy.

At birth (V3), maternal characteristics (including mode of delivery, gravidity, parity, etc) and neonatal characteristics (including gestational age, sex, weight, length, etc) will be assessed. A sample of umbilical cord blood will be collected to measure various biomarkers, including glucose, insulin, total cholesterol, low-density lipoprotein (LDL)-cholesterol, high-density lipoprotein (HDL)-cholesterol, triglycerides, uric acid, creatinine, hs-CRP and various miRNA.

An echocardiography will be done to assess cardiac structure (including LVMI) and function 2–7 days after birth (V4). cIMT will be measured to assess vascular structure.

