**Figure 1 F1:**
[figure not shown]
Hypothetical and highly simplified causal relationships between gestational diabetes mellitus (GDM) and cardiometabolic disorders. Two pathways can be hypothesised: (1) a direct effect of GDM on offspring’s cardiometabolic disorders; (2) an indirect effect through the mediator large for gestational age (LGA). It means that if LGA was prevented, part of the effect of GDM on cardiometabolic disorders would be prevented. Several confounding factors (such as maternal obesity, weight gain during pregnancy, smoking, socioeconomic status or family history of cardiometabolic diseases) have to be accounted.

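### GDM treatment is listed as a confounder of the GDM–outcome regression although it follows GDM; with it in the model, the GDM coefficient no longer estimates the total effect of GDM

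*Protocol article*

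**What the plan says.** All references are to the protocol article.

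- **Statistical analysis, model:** "The association between exposure (GDM/no GDM) and the (continuous) outcomes will be estimated with linear regression analyses".
- **Statistical analysis, adjustment:** the parenthesis of potential confounders ends "personal history of CVD, treatment for GDM during pregnancy) will be done".
- **Statistical analysis, last sentence:** "We will also consider the effect of treatment which will be treated as a mediator between GDM, LGA and outcomes".
- **Data collection and visits:** "In women with GDM, information about treatment and blood glucose measurements will be recorded during the whole pregnancy".
- **Objectives:** "Our objectives are to assess the effect of GDM on offspring’s cardiovascular health early in life".
- **Figure 1 caption:** "Several confounding factors (such as maternal obesity, weight gain during pregnancy, smoking, socioeconomic status or family history of cardiometabolic diseases) have to be accounted". Treatment is not among these examples.

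The article does not distinguish a model for the total effect, without treatment, from a model for a direct effect, with treatment.

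**The concern.** A confounder of the GDM–outcome association has to be a cause of GDM, or share a cause with it, and must not be a consequence of it. Treatment for GDM is a consequence: it starts after the diagnosis and does not occur without it. Adjusting for it as a confounder removes part of what GDM, as managed, does to the child, and changes which women the coefficient describes.

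The listed covariates apply to the regressions for both primary outcomes, LVMI and cIMT. Two analysts could both follow the paragraph, one with treatment in the regression and one keeping it for the mediation step, and report different numbers as the GDM effect from the same data.

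**Working it through.** **1. The plan's own sample size.** The Sample size section gives the inputs: "Assuming that LVMI will be 30 g/m^2.7^(SD: 4.5) in children of mothers without GDM" and "compared with 32 g/m^2.7^(SD: 4.5) in children of women with GDM", so a difference of 2 with SD 4.5, two-sided alpha 0.05 and power 80%.

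n per group = 2 × (1.960 + 0.842)² × 4.5² / 2² = 79.5, rounded up to 80. Allowing for 20% loss, 80 / 0.8 = 100. Both stated figures reproduce and are not in dispute. They rest on the contrast of all GDM with all non-GDM offspring.

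**2. What the coefficient becomes.** Let G = 1 for GDM and T = 1 for treated. T is 0 whenever G = 0, so only three groups exist: no GDM, untreated GDM and treated GDM. In the model outcome = a + b·G + c·T, before other covariates:

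- a = mean without GDM
- a + b = mean in untreated GDM
- a + b + c = mean in treated GDM

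Hence b is untreated GDM minus no GDM. With a share p of GDM women treated, the whole-group contrast is b + p·c. The two agree only if p = 0 or c = 0.

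**3. Direction.** Fix the whole-group contrast at 2.0 and take two assumed scenarios:

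- (a) Treatment lowers LVMI by 2, so c = −2 and b = 2 + 2p.
- (b) Treatment does nothing but goes to the more severe cases, with severity standard normal and a slope of 1 g/m^2.7 per SD. Then b = 2 minus the amount by which mean severity in the untreated falls below zero.

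| Share treated (assumed) | b in (a) | b in (b) |
|---|---|---|
| 30% | 2.6 | 1.5 |
| 50% | 3.0 | 1.2 |
| 70% | 3.4 | 0.8 |

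The coefficient moves up in one scenario and down in the other. Large-sample least-squares simulation gave the same values.

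**4. Precision.** SE(b) = 4.5 × √(1/80 + 1/(80(1 − p))), and power for a difference of 2 is Φ(2/SE − 1.96), a normal approximation. Example at p = 0.5: SE = 4.5 × √(1/80 + 1/40) = 0.871; 2/0.871 − 1.96 = 0.335; power 63.1%.

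| Share treated (assumed) | Untreated GDM women | SE | Power |
|---|---|---|---|
| 0% (same as omitting the term) | 80 | 0.712 | 80.3% |
| 20% | 64 | 0.755 | 75.5% |
| 30% | 56 | 0.784 | 72.3% |
| 50% | 40 | 0.871 | 63.1% |
| 70% | 24 | 1.047 | 48.0% |
| 80% | 16 | 1.232 | 36.8% |
| 90% | 8 | 1.669 | 22.3% |
| 100% | 0 | – | not estimable |

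At 100%, T equals G: the design matrix has rank 2 for 3 columns.

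For cIMT (difference 0.02 mm, SD 0.04), the same formula gives 88.5% without the term, about 73% at p = 0.5 and about 45% at p = 0.8.

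**The case against.** The best defence is that treatment has a legitimate place in this study and the article gives it one. It commits to causal mediation analysis with treatment on the path between GDM, LGA and outcomes, and the contrast of untreated GDM with no GDM is a direct-effect quantity that can be interpreted if confounding of treatment and outcome is handled. The Objectives also do not say in so many words that the total effect is meant. All of that stands. It does not rescue the adjusted regression, because the article puts treatment there as a confounder, and the contrast that results is not the one used for planning.

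A reader might go further in several ways that the article does not support:

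- **That a variable cannot be both mediator and confounder.** It can mediate GDM to outcome and confound LGA to outcome. What it cannot be is a confounder of GDM to outcome.
- **That the estimate is biased towards zero because untreated cases are milder.** The article does not say how treatment is assigned, and the direction is open, as step 3 shows.
- **That a known, large amount of power is lost.** The share treated is not reported. At 20% to 30% the loss is modest.
- **That the coefficient will be inestimable.** This happens only if treatment is defined so that every GDM woman has it, and the article does not define it.
- **That the mediation analysis is invalid.** Treatment being zero in the unexposed does not by itself defeat mediation, and the choice of estimator belongs to an analysis plan that is not shown.

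The article also says that baseline biomarkers will be treated as potential confounders, and glucose and HbA1c are measured at the first visit. Scenario (b) has no such adjustment, so it illustrates the mechanism and does not predict the result. Adjusting for glycaemia would still leave b as a conditional contrast of untreated GDM with no GDM.

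**Conclusion.** The point holds. Listing treatment among the confounders of the GDM–outcome regression is wrong as written, it conflicts with the mediator role given in the same paragraph, and no other part of the article resolves it. The consequence is limited to this: the adjusted GDM coefficient would no longer estimate the total effect of GDM, for either primary outcome.

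That conclusion needs only that treatment follows the diagnosis and is absent in women without GDM. The size does depend on assumptions. The treated share is assumed throughout, the shift in the coefficient rests on the two illustrative scenarios, and the power figures assume a common SD of 4.5, a true untreated-versus-none difference of 2 and no other covariates. They are a range that shows what is at stake, not a separate finding.

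**What to change.** Delete the treatment term from the parenthesis of confounders in the Statistical analysis section, and state that the adjusted regression of outcome on GDM estimates the total effect of GDM. Keep treatment in the mediation analysis, or in a secondary analysis labelled as such, for example a comparison within women with GDM that adjusts for glucose at diagnosis.

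Cost: one phrase in the text and a little analysis work. Treatment and glucose are already to be recorded in women with GDM, so no new data are needed, and the sample size is unchanged.

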**Figure 1 F1:**
[figure not shown]
Hypothetical and highly simplified causal relationships between gestational diabetes mellitus (GDM) and cardiometabolic disorders. Two pathways can be hypothesised: (1) a direct effect of GDM on offspring’s cardiometabolic disorders; (2) an indirect effect through the mediator large for gestational age (LGA). It means that if LGA was prevented, part of the effect of GDM on cardiometabolic disorders would be prevented. Several confounding factors (such as maternal obesity, weight gain during pregnancy, smoking, socioeconomic status or family history of cardiometabolic diseases) have to be accounted.

## Ethics and dissemination

The study poses little to no risk to participants and their offspring. Signed informed consent is obtained from all participating women. Participation in the study does not interfere with the typical care patients receive during pregnancy and after delivery. Clinicians in the obstetrical clinic provide clinical follow-up and, if necessary, participants are referred on for additional clinical management.

Results from this study will be disseminated at regional and international conferences and in peer-reviewed journals.

## Significance and outlook

The current high prevalence of maternal obesity and associated hyperglycaemic disorders may lead to a perpetuating intergenerational cycle of increasing obesity, metabolic and cardiovascular disorders. Well-designed prospective studies are necessary to better quantify the actual impact of maternal hyperglycaemic disorders on offspring’s health and to identify the potential underlying mechanisms. Despite recent significant advances in DOHaD and foetal programming research, major challenges have to be addressed, notably by better objectively characterising both early life exposure and cardiometabolic outcomes.^23^

Indeed, many past studies on the foetal programming of cardiometabolic disorders suffered from some methodological flaws including confounding, no or poor standardisation of exposure and outcome assessment, and selection bias. Our prospective population-based study in pregnant women whose offspring is examined during fetal life and at birth avoids some of these issues. The long period needed for CVD to develop could be a limitation, but this will be overcome in our study by measuring surrogate outcomes (including LVMI and cIMT) that are well-established precursors of CVD.^31^ In addition, a long-term follow-up of the offspring is planned (not funded yet) for further assessment of their cardiovascular health.

By looking at the fetomaternal circulation, foetal cardiovascular system and liver and foetal growth and CVD risk markers at birth, we will acquire unique data to gain insight in the early mechanisms underlying the development of CVD and metabolic diseases and on the role of maternal hyperglycaemic disorders. GDM is an opportunity for timely intervention for the prevention of cardiometabolic disorders in mothers and their offspring.^9^ With the new criteria to define GDM, a growing proportion of women will be concerned by this disorder. Having a better understanding of the clinical impact of maternal hyperglycaemic disorders on offspring’s health early in life is urgently needed to inform strategies for the early prevention of CVD.
